### Outcomes

Primary outcomes: rMT (%), CSP (ms), MEP latency (ms) and amplitude (mV), CMCT (ms), SICI (ratio), and ICF (ratio). Secondary outcomes: correlation between TMS metrics (primary outcomes) and psycho-cognitive measures (Vocabulary subtest of the Wechsler Adult Intelligence Scale; Global Sleep Assessment Questionnaire; Pittsburgh Sleep Quality Index; Beck Depression Inventory II; State-Trait Anxiety Inventory).

### Statistical analysis

After the analysis of descriptive statistics, based on the results of the Shapiro–Wilk normality test, each outcome will be compared across the three treatment conditions by a repeated-measures ANOVA (if data are normally distributed) or the nonparametric Friedman ANOVA (if data are not distributed normally). After the completion of the data collection, a power analysis will be carried out in order to check if the statistical power of at least 80% is achieved and plan an eventual study extension is needed or not. In any case, the planned number of patients will allow to obtain a power of 80% (with alpha 0.05) even with a “moderate” effect size, as small as 0.465 [44]. No missing data are expected because we plan to continue the recruitment until we reach a number of 30 participants with a complete research protocol.

Fig 2 illustrates the flow chart and main procedures of the study protocol.

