Based on these considerations, a combination of dipyridamole and caffeine in the modulation of adenosine system, in both directions (i.e., up- or down-regulation, respectively), might be apply for a new and “pharmaco-TMS”-based treatment of RLS. Therefore, in this pilot study protocol, we aim to analyze the differential effects of dipyridamole and caffeine, compared to a placebo, on a number of specific measures of cortical excitability to TMS in patients with primary RLS. Initial assessments will include single- and paired-pulse TMS to evaluate cortical excitability. Then, based on the obtained measures, we will investigate the effects of dipyridamole and caffeine on TMS parameters of cortical excitation and inhibition in RLS patients. Lastly, we will assess psycho-cognitive performance in RLS patients to screen them for cognitive impairment and/or mood-behavioral dysfunction, which will eventually allow to correlate psycho-cognitive scores and TMS data.

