## Materials and methods

### Study design

The study employs a double-blind, randomized, cross-over exploratory design. Each subject will receive dipyridamole, caffeine, or a placebo in a random sequence determined by computer-generated random numbers. The administration will occur during three different TMS sessions in the late afternoon (in accordance with the circadian distribution of RLS symptoms), with a sufficient wash-out period (at least 2 times the half-life of each substance) between sessions. To enhance the randomness of the sequence, planned restrictions will be unavailable to the contributors enrolling participants or assigning interventions. The allocation sequence will be implemented using sequentially numbered, opaque, sealed envelopes. Blinding of trial participants, outcome assessors, and data analysts will be maintained also after assignment to interventions.

This study (version v.1.0_14/07/2020) received approval from the research Ethics Committee “CE IRCCS Sicilia – Oasi Maria SS.” on October 25, 2016 (Approval ID: 2016/CE-IRCCS-OASI/1). It adheres to SPIRIT (Standard Protocol Items for Randomized Trials) recommendations in a clinical trial protocol and related documents (Fig 1), and it has been registered in a WHO approved registry, i.e., the ISRCTN registry (registration number: ISRCTN11559397). Any protocol amendments or relevant modifications (such as changes to eligibility criteria, outcomes, analyses) will be communicated to relevant parties, including investigators, the research Ethics Committee, trial participants, trial registries, journals, and regulators. The recruitment period for this study will range from March 01, 2024, to February 28, 2025. Written informed consent will be signed by all subjects prior to the inclusion in the study; additional consent provisions for participant data collection and use will be obtained, if necessary. Authorship eligibility of protocol contributors will follow the guidelines of the International Committee of Medical Journal Editors (ICMJE).

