### Assessment

This is a single center, double blind, randomized, 3-period 3-treatment, random-sequence crossover study. After the baseline TMS assessment, the same participants will be orally exposed to all substances (dipyridamole, caffeine, or placebo), in a random order, after a washout period. Participants and researchers involved will be blind to the substance’s nature. More in details, the “dipyridamole arm” will consist of a single oral dose of dipyridamole 75 mg, while the “caffeine arm” of a single oral dose of caffeine 200 mg. After an approximately one-hour interval (the absorption peak of dipyridamole and caffeine is known to occur in about 60 minutes after the oral intake), TMS tests will be repeated to evaluate potential effects of the active compounds compared to placebo. All capsules (active and placebo), prepared by the Pharmacy Department of the Oasi Research Institute-IRCCS, will be indistinguishable. Clinical evaluation and IRLS-RS will be repeated after each experimental condition. Discontinuation or modification of interventions will be allowed, if necessary (e.g., dose change in response to harms or worsening disease), and all the procedures needed to improve adherence to intervention protocols and monitoring will be taken into account. There will be no other relevant or concomitant treatment during the interventions.

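### Every outcome gets one omnibus three-condition test, with no period term and no drug-placebo contrast, so the stated question is not answered and any drift between sessions costs power

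*Protocol article*

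**What the plan says.** The Assessment section of the protocol article describes a "3-period 3-treatment, random-sequence crossover study". The Study design section says that patients receive the three substances "in a random sequence determined by computer-generated random numbers". On restriction of the randomisation it adds only that "planned restrictions will be unavailable to the contributors enrolling participants or assigning interventions", without describing the restrictions.

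The aim appears twice. In the Introduction: "we aim to analyze the differential effects of dipyridamole and caffeine, compared to a placebo". In the Assessment section: "TMS tests will be repeated to evaluate potential effects of the active compounds compared to placebo".

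The Statistical analysis section fixes the test: "each outcome will be compared across the three treatment conditions by a repeated-measures ANOVA (if data are normally distributed) or the nonparametric Friedman ANOVA". The choice between the two depends on a Shapiro–Wilk test. No period or sequence term is named, and no pairwise comparison. The same section claims 80% power at alpha 0.05 for an effect size of 0.465, and says that "we plan to continue the recruitment until we reach a number of 30 participants with a complete research protocol".

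**The concern.** There are two separate problems.

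**The question.** The aim is two differences, each drug minus placebo. The named test asks whether three means (or rank sums) are all equal. Rejecting that hypothesis does not say which drug is responsible, and it gives no estimate or interval for either drug. The Introduction treats the two drugs as moving the adenosine system in opposite directions, so the dipyridamole–caffeine difference can contribute much of the omnibus signal although it is not the stated comparison.

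**The period.** Each patient has three post-dose TMS sessions. If the measures change systematically from session to session, for example through habituation, a one-factor repeated-measures ANOVA cannot separate that change from noise. The Friedman test ranks within patient and has no place for period either. At stake are the power and the width of the intervals for all seven primary TMS measures.

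**Working it through.** **The plan's own figure.** A paired t-test with n = 30 and a standardised paired difference (dz) of 0.465 has noncentrality 0.465 × √30 = 2.55 on 29 df. One-sided at 0.05 its power is 80.0%, which matches the plan. Two-sided it is 69.2%, and 80% then needs dz = 0.529. The three-level repeated-measures ANOVA with 0.465 read as Cohen's f gives 89% or more, depending on convention and correlation. Of the readings tried, only the two-condition comparison reproduces the claim, and the analysis section never names such a comparison.

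**Inputs for the period check.** From the article: n = 30 completers, three periods, three treatments, alpha 0.05. Assumed: within-patient SD σ = 1; one drug differs from placebo by dz = 0.53 (the two-sided 80% value above), that is by 0.53√2 on the σ scale, and the other drug does not differ; session effects are 0, δ and 2δ, with δ from 0 to 0.75. The article gives no value for δ.

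**Omnibus power without drift.** λ = n Σ(τ − τ̄)²/σ² = 30 × (2/3) × (0.53√2)² = 30 × (2/3) × 0.5618 = 11.24. The critical value of F(2, 58) is 3.156, and the noncentral F gives 84%.

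**Effect of drift.** Centred on the patient's mean, the session effects are −δ, 0 and δ, a sum of squares of 2δ² per patient.
- *Simply random orders:* the treatment and error mean squares both rise by δ² in expectation. The test keeps its size and λ becomes 11.24/(1 + δ²).
- *Balanced orders:* all of it falls into error, which becomes 1 + 30 × 2δ²/58 = 1 + 1.034δ². The treatment mean square is unaffected, so the critical value is in effect multiplied by that factor.

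| δ (within-patient SD per session) | Random orders: 1 + δ² | Power | Balanced orders: 1 + 1.034δ² | Power | Type I error |
|---|---|---|---|---|---|
| 0 | 1.00 | 84% | 1.00 | 84% | 5.0% |
| 0.25 | 1.06 | 82% | 1.06 | 82% | 4.2% |
| 0.5 | 1.25 | 75% | 1.26 | 75% | 2.4% |
| 0.75 | 1.56 | 64% | 1.58 | 64% | 1.0% |

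Simulation over both kinds of order agrees: 83–84%, 81–82%, 73–75% and 64–65%. With simply random orders, simulated type I error of the plain ANOVA was 4.8% at δ = 0.5 and 5.3% at 0.75.

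**With a period term.** The error df fall from 58 to 56. With balanced orders, power is 84% whatever the drift. Across balanced and random orders, simulation gives about 80–84% throughout.

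**Role of balance.** For one drug-placebo contrast in units of the paired-difference SD, the standard error with a period term is about 0.185 with random orders and 0.182 with balanced ones. Without a period term, at a drift of 0.5 paired-difference SD per session (about 0.71 within-patient SD), it is about 0.222 and 0.224. The period term recovers the precision; balance alone does not.

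**The case against.** The case for the plan is that it is an exploratory pilot reported in a condensed article. Pairwise follow-up and model details often sit in an analysis plan that is not shown, and nothing in the article forbids a placebo comparison. The drift is assumed, and at 0.25 SD per session or less almost nothing is lost. A mixed model is also partly a matter of taste: with complete data, a within-patient ANOVA that includes period would do as well.

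Much of this stands. The power loss is conditional, and the kind of model matters less than its terms. But the article does not defer the method. It names the test for each outcome, and that test does not deliver the comparison the article states as its aim.

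Four stronger readings are tempting and are not supported:
- *That the sequences are unbalanced.* The article mentions planned restrictions without describing them, so neither balance nor its absence is established. Probabilities computed for unrestricted allocation would describe a scheme the article does not state.
- *That false positives are inflated or the estimates biased.* With random orders type I error stays near 5%, and with balanced orders the test is conservative.
- *That a significant omnibus result may mean neither drug truly differs from placebo.* If both drugs equalled placebo, all three means would be equal. Type I error apart, rejection implies that at least one differs; it leaves open which one.
- *That non-significant contrasts after a significant omnibus test show the test misleading.* With true opposite effects of 0.25 SD each, such results reflect the low power of real contrasts, which the proposed model would share.

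**Conclusion.** The point holds in this form: the article fixes an omnibus test without a period term and without the two drug-placebo contrasts that its aim requires. The mismatch with the aim rests on the text alone and needs no assumption.

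The loss from omitting period depends on drift that the documents do not quantify. With n = 30 and dz = 0.53 it is nil without drift, about 1 to 3 percentage points of power at 0.25 within-patient SD per session, 7 to 9 at 0.5 and 18 to 20 at 0.75. These figures assume a linear drift, normal errors and an effect of one drug only. No claim is made about balance of the sequences, bias or excess false positives. The change should be made before the data are analysed, because it costs almost nothing when there is no drift and protects power when there is.

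**What to change.** Analyse each outcome with a model that has treatment and period as fixed effects and patient as a random or fixed effect. Make dipyridamole minus placebo and caffeine minus placebo, each with a 95% confidence interval, the primary estimates; the omnibus test can stay as a secondary summary. The Friedman test takes no period term, so say what replaces it when normality fails, for example the same model on a log scale. State the power for the named contrasts, with sidedness and type of effect size, and state the set of sequences and the restriction used.

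The cost is two degrees of freedom for period (58 to 56) and a change of analysis wording. No extra patients, visits or measurements are needed.

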### Participants

Patients will be recruited from a community clinic at the Department of Neurology IC and Sleep Research Center of the Oasi Research Institute-IRCCS in Troina (Italy), upon their first diagnosis. They must meet all the inclusion criteria and none of the exclusion criteria, whether as out-patients or in-patients. Recruitment and clinical assessment will be supervised by a trained neurologist expert in sleep medicine and disorders ([name]). Given the novelty of the study, sample size calculation relies on similar articles in the literature and the typical sample size in TMS research, indicating a minimum of 30 *de novo*, drug-free, patients. All strategies for achieving participant enrolment to reach target sample size will be adopted, as well as plans to promote participant retention and follow-up completion.

Inclusion criteria will be: i) age 18-65 years; ii) diagnosis of RLS according to the latest criteria by the International RLS Study Group [34]; iii) RLS symptoms on 3 or more days per week for at least 3 months; iv) International RLS Rating Scale (IRLS-RS) score >15 (i.e., moderate symptomatology, at least); v) normal brain magnetic resonance imaging (MRI) and upper limb electromyography (EMG), including the study of the F-waves; vi) women of childbearing potential must have a negative pregnancy test and agree not to become pregnant during the whole experimental procedure; vii) personally signed and dated informed consent obtained before any procedure. All personal information about potential and enrolled participants will be collected and maintained, in order to protect confidentiality before, during, and after the whole procedure.

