
Potential limitations of this study protocol include:

TMS may not provide disease-specific pathophysiological information, although it is sensitive to various neurotransmitters and cortical-subcortical motor inputs; therefore, instead of seeking a single marker of the disease process, the study will aim to identify a distinctive panel of measures [47], potentially allowing the identification of neurophysiological indexes related to adenosine responders;the study will be conducted in the awake state, differing from the sleep condition; however, as previously reviewed [19,21,22], most studies, even the most recent ones, are performed during wakefulness, likely due to technical/procedural reasons;the use of a hand muscle in RLS subjects might be considered inadequate, although TMS measures have shown involvement even when recording over hand muscles [19,21]; moreover, technical difficulties of MEPs recordings from lower limbs may affect the reliability and reproducibility of results;the minimum number of participants cannot be determined through statistical sample size/power analysis due to the novelty of the proposal and the lack of previous data, although comparable numbers of participants are common in TMS literature; nevertheless, if preliminary data analysis will suggest the need to increase the total sample size beyond 30 after recruiting the first 10-15 patients, it will be done without further funding requests;the possibility of a “placebo effect” cannot be entirely excluded, but it is expected to do not to persist over time.

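### Extension of the trial is tied to a power check on the collected data and to an undefined early look; the first is circular or empty, and neither has a stated rule

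*Protocol article*

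**What the plan says.** The Protocol article has two routes to a larger trial.

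- **After data collection (Statistical analysis).** "a power analysis will be carried out in order to check if the statistical power of at least 80% is achieved", and the result serves to "plan an eventual study extension is needed or not".
- **Early look (Expected results, potential limitations).** The sample may grow "if preliminary data analysis will suggest the need to increase the total sample size beyond 30 after recruiting the first 10-15 patients".

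The base sample is described in several ways. Participants cites the literature as "indicating a minimum of 30". Statistical analysis says "we plan to continue the recruitment until we reach a number of 30 participants with a complete research protocol". That section also claims, unconditionally, that "the planned number of patients will allow to obtain a power of 80% (with alpha 0.05") for an "effect size, as small as 0.465", whereas the limitations say that the number could not be derived from a power calculation.

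Each outcome is to be compared across the three conditions by repeated-measures ANOVA or the Friedman test. The only alpha in the article is the 0.05 in the power statement. Study design says that data analysts stay blinded after assignment. Neither extension route states which effect size or variance enters the calculation, which outcome drives it, a maximum sample, or how results before and after the extension are combined.

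**The concern.** A power figure computed from the effect just observed adds nothing to the p-value. Used as a trigger, it makes the decision to recruit more patients depend on how significant the result already is. If treatment-effect data steer the sample size and the last test is still read at 0.05, the false-positive rate can exceed 5%. How far depends on what happens to a result that is already significant, and the article does not say. The early look has the same problem if it uses the treatment effect, and none if it uses only pooled variance. At stake is whether the reported p-values mean what they appear to mean, and whether further patients are recruited for a sound reason.

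**Working it through.** **Inputs from the article.** 30 completers; three conditions within patient ("3-period 3-treatment, random-sequence crossover study"); alpha 0.05; target power 80%; effect size 0.465, metric not stated; early look at 10-15 patients. **Assumed, because the article gives none:** extended samples of 40, 45 or 60, and caps of 60 or 120 for the early look.

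**Step 1. The plan's own figure.** For a paired t-test the noncentrality is 0.465 × √30 = 2.547 on 29 df. Power is 0.800 one-sided and 0.692 two-sided at 0.05. The stated 80% therefore reproduces as a one-sided paired comparison. Reading 0.465 as Cohen's f for the three-condition ANOVA gives 0.977 or more. Any such calculation with a fixed effect size can be done now and needs no trial data.

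**Step 2. Observed power at n = 30.** For the omnibus F test on 2 and 58 df, the 5% critical value is 3.156. Observed power is P[F′(2, 58; λ) > 3.156] with λ = 2 × F_obs, so it is a function of F_obs alone, and hence of p.

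- p = 0.05: F_obs = 3.156, λ = 6.31, observed power 0.58.
- Observed power 0.80: F_obs = 5.075, λ = 10.15, p = 0.0093.

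A check for 80% observed power is thus a check for p at or below about 0.009. Under the null, 1 − 0.0093 = 0.99 of trials fall short and would be extended. That includes trials with p between 0.009 and 0.05, which are significant at the nominal level.

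**Step 3. Type I error for one outcome.** Simulation of 200,000 null trials, repeated-measures ANOVA at nominal 0.05, Monte Carlo standard error about 0.0005. The fixed design with 30 patients gives 0.051.

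| Reading of the rule | Type I error |
|---|---|
| Extend whenever observed power is below 80%; only the final test counts (to 40 / 45 / 60) | 0.053 / 0.053 / 0.055 |
| Effect-based increase after 10 / 15 patients, one final test, cap 60 | 0.059 / 0.061 |
| Same, cap 120 | 0.063 / 0.067 |
| p < 0.05 at 30 stands; otherwise extend and retest (to 40 / 45 / 60) | 0.076 / 0.079 / 0.085 |

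For the early look, the sample was set from the observed F at the look (n1 patients) to reach a noncentrality of 9.9, that is N = 9.9 ÷ (2F/n1), never below 30 or above the cap.

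**Step 4. Controlled alternatives, same simulation.** A blinded variance-only re-estimation at 15 patients (to 30 or 60) with one final test at 0.05 gives 0.051. Testing at 30 and again at 60, each at 0.0294 (Pocock), also gives 0.051.

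**The case against.** Four arguments favour the plan.

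- **The article does not say that the observed effect is used; observed variability could be the input.** This is fair, and a variance-only version would be harmless. But 0.465 appears to be a standardised effect, which a new variance estimate leaves unchanged. A variance update needs a target difference in outcome units, and none is given. With 0.465 itself, the plan says the answer is already known.
- **Analysts are blinded.** The Study design statement counts, but it does not settle the matter. The ANOVA and Friedman statistics do not change when treatments are relabelled, so an analyst who sees only coded conditions can still obtain F, p and observed power.
- **The trial is a pilot, labelled exploratory, and an analysis plan not shown may supply the cap and the alpha rule.** This lowers the consequence, and the missing details are not held against the article. The point rests on what the article does fix: a power check after data collection as the trigger for extension.
- **Under the most literal reading the inflation is slight.** This stands, at 5.3-5.5%.

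A reader might infer more: significance tests at 15, 30 and later samples, any of which could declare success. The documents do not support that. The early look mentions neither a hypothesis test nor stopping for success, and recruitment is to continue to 30 completers. Nor should the error over all seven primary outcomes be charged to the extension. Seven independent tests at 0.05 already give 1 − 0.95^7 = 0.30 with no extension, and that is a separate matter.

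**Conclusion.** The concern holds in a limited form. The power check after data collection is unsound as an extension trigger: circular if it uses the observed effect, without content if it uses 0.465. The early look is left open to an effect-based increase.

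The size of the harm is conditional. Type I error per outcome is about 5.3-5.5% on the power-triggered reading with one final test, about 6-7% for an effect-based increase at 10-15 patients, and about 7.5-8.5% only if significance at 30 is allowed to stand and other trials are retested. The article does not commit to that last rule. All figures rest on the assumed extended samples and caps above.

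A flat statement that p-values and intervals from an enlarged sample are invalid would go too far, given the first of these figures. Severity is moderate.

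**What to change.** 1. Delete the power analysis after data collection as a trigger for extension, and report 95% confidence intervals for the treatment contrasts.
2. Either fix the sample at 30 completers, or replace both provisions with a single blinded re-estimation at 15 patients. Base it on the pooled within-patient variance, with no treatment contrast or F test computed, a target difference in outcome units, a named outcome and a stated maximum sample. Follow it with one final test at 0.05; no alpha adjustment is then needed.
3. If an effect-based extension is wanted, prespecify a combination test or a group-sequential boundary, with the looks and the maximum sample.
4. Remove the open reference to a preliminary data analysis, and align the statements on whether 30 is a minimum or a fixed number and whether it rests on a power calculation.

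The cost is a change of wording made before any results are seen. The sponsor gives up the freedom to extend after looking at the data.

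### The stated 80% power at effect size 0.465 names no test or metric; it matches a one-sided paired t-test that is not planned, and on that scale the planned three-condition ANOVA has about 60% to 73%

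*Protocol article*

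**What the plan says.** The Statistical analysis section of the Protocol article plans one kind of comparison: "each outcome will be compared across the three treatment conditions by a repeated-measures ANOVA (if data are normally distributed"). For outcomes that fail the normality check, a Friedman test takes its place. The Assessment section describes the design: "This is a single center, double blind, randomized, 3-period 3-treatment, random-sequence crossover study". The Outcomes section lists seven primary TMS measures.

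The Statistical analysis section then says, introduced by *In any case*, that this sample size "will allow to obtain a power of 80% (with alpha 0.05) even with a “moderate” effect size, as small as 0.465". It does not say which test this refers to, whether it is one- or two-sided, or whether 0.465 is a d, a dz or an f. The number analysed is fixed by completers: "we plan to continue the recruitment until we reach a number of 30 participants with a complete research protocol".

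The limitations listed under Expected results say that "the minimum number of participants cannot be determined through statistical sample size/power analysis", because the proposal is new and earlier data are lacking. The Participants section takes the figure of 30 from similar articles and from the usual size of TMS studies.

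**The concern.** A power statement has to belong to the test that will be run. Here the planned test is an F test or a Friedman test across three conditions, and neither has a direction. The figure of 0.465 corresponds most closely to a directional comparison of two conditions, which appears nowhere in the protocol. If that is its origin, the detectable effect is stated too favourably for the planned analysis.

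This is the protocol's only quantitative statement about what 30 patients can show. The protocol also provides for power-based decisions about extending the study, so an optimistic benchmark could make 30 look sufficient. A non-significant result could also be taken as stronger evidence against moderate effects than it is.

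**Working it through.** **Inputs from the protocol.** n = 30 completers, each receiving three conditions; alpha 0.05; power 80%; effect size 0.465 (all from Statistical analysis and Assessment).

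**Assumptions, since the protocol gives no SD, correlation or metric.** 0.465 is read as dz (mean paired difference divided by the SD of the paired differences), taken as the largest pairwise difference, with sphericity. Other readings follow in step 4.

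**1. Reproducing the stated figure.** For a paired t-test the noncentrality is dz × √n = 0.465 × √30 = 2.547, with 29 df.
- One-sided alpha 0.05 (critical t 1.699): power 80.01%. The dz giving exactly 80% is 0.46495, which rounds to 0.465.
- Two-sided alpha 0.05 (critical t 2.045): power 69.2%. The dz giving 80% is 0.529.

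Other candidates miss 0.465: normal approximations give 0.454 (one-sided) and 0.511 (two-sided), and a one-sided Wilcoxon test by asymptotic efficiency gives 0.476.

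**2. The planned repeated-measures ANOVA.** The test is F with 2 and 58 df, critical value 3.156. Scale the SD of a paired difference to 1. Under sphericity the error variance is then 1/2, and λ = n × Σ(mean − grand mean)² ÷ (1/2) = 60 × Σ(mean − grand mean)².

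| Pattern of means, d = 0.465 | Σ | λ | Power |
|---|---|---|---|
| Third condition midway (−d/2, 0, d/2) | d²/2 | 30d² = 6.49 | 59.6% |
| One condition differs (0, 0, d) | 2d²/3 | 40d² = 8.65 | 72.9% |

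Eighty per cent power needs λ = 10.15. The detectable dz is therefore √(10.15/30) = 0.582 for the first pattern and √(10.15/40) = 0.504 for the second. With a sphericity epsilon of 0.75, the two powers fall to 51.2% and 63.8%.

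**3. The planned Friedman alternative.** Simulation with normal data (20,000 runs, same patterns) gives about 48% and 60%.

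**4. Readings on which power is higher.**
- *Drugs moving in opposite directions*, each 0.465 from placebo, so that the largest difference is 0.93: λ = 120d² = 25.95, power 99.6%.
- *Cohen's f on the total-variance convention*, λ = 90f²/(1 − ρ): power at f = 0.465 is 97.7% or more for ρ from 0 to 0.8. The f detectable at 80% is 0.336 (ρ = 0), 0.237 (ρ = 0.5) or 0.150 (ρ = 0.8).
- *Cohen's f from partial eta-squared*, λ = 58f²: power at 0.465 is 88.0% under sphericity, where the f detectable at 80% is 0.418. With epsilon 0.75 the power is 80.1% and the detectable f is 0.464.
- *Difference in raw SD units*: ANOVA power runs from 33% to 73% for ρ from 0 to 0.5, and is 83% or more for ρ of 0.7 and above.

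**The case against.** The protocol never says that it used a one-sided paired t-test. The source cited for 0.465 is not available here, and the basis is reconstructed from a numerical match. Another route comes close: f from partial eta-squared gives about 80% at 0.465 for the planned ANOVA if epsilon is 0.75. The trial's rationale also has the two drugs shifting the adenosine system in opposite directions, and that is the pattern in which the ANOVA has ample power. Finally, this is an exploratory pilot whose size rests on similar studies, not on this sentence.

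Most of this stands as a limit on the claim. The one-sided test cannot be reported as fact, and the shortfall depends on how 0.465 is read. It does not rescue the sentence. The partial eta-squared match needs an epsilon that the protocol does not mention; under sphericity, both f conventions make 0.465 larger than the smallest detectable effect. The opposite-direction pattern is one possibility among several and cannot support an unconditional assurance. The raw-SD reading depends on a correlation that is not given.

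A reader might also infer that the Statistical analysis section contradicts the limitations list. It need not. Saying that n could not be derived from a power analysis is compatible with saying what a fixed n of 30 can detect. Nor do power figures at a divided alpha belong here. The protocol states 0.05 and plans no division, so multiplicity over seven outcomes is a separate question.

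**Conclusion.** The point holds in conditional form. The power sentence does not identify its test, sidedness or metric, and the closest match found is a one-sided two-condition test outside the plan. On the scale that reproduces 0.465 (largest pairwise dz, sphericity, n = 30, alpha 0.05), power is 69% for a two-sided paired contrast and about 60% to 73% for the planned ANOVA, against the stated 80%. The detectable dz is 0.53 and 0.50 to 0.58 respectively.

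It would go too far to conclude that the trial is underpowered or that 30 patients are too few. The documents do not fix the metric or the pattern of means, and some readings give power well above 80%. What fails is the unconditional wording together with the description of 0.465 as the lower limit of what can be detected.

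**What to change.** Rewrite the power sentence in the Statistical analysis section for the planned test or for a named two-sided contrast. Possible wording:

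*With 30 completing participants, power is 80% at two-sided alpha 0.05 for a within-patient standardised difference (dz) of about 0.53 in one drug–placebo contrast of one outcome. For the three-condition repeated-measures ANOVA under sphericity, the corresponding largest pairwise dz is 0.50 to 0.58, depending on the pattern of means.*

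State that the metric is dz. Delete *In any case*. Add that this is a sensitivity statement for a fixed n of 30 and not the basis for choosing n, which brings it into line with the limitations list. If the authors did use a different test or metric, they should name it and give its assumptions, including the within-patient correlation or epsilon.

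The cost is a text change. No extra patients or procedures are needed, but the stated detectable effect becomes less favourable.
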